### Rules for syntactically improving physician provided search queries

1. Update MeSH terms indicated as exploded terms and add PubMed syntax for limits described

2. Correct spelling errors

3. Capitalize Boolean terms (AND, OR, NOT)

4. Remove commas ',' periods '.' semi-colons ';' and apostrophes "'"

5. Replace '/' with an OR term

6. Replace 'and/or' with an OR term

7. Replace '+' with an AND term

8. Remove preposition and article terms (e.g. 'in,' 'by,' 'at,' 'for,' 'from,' 'a,' 'the')

9. Expand short forms or acronyms and include the original term with an OR term

The use of filters for subject areas (methods or renal information) is advantageous, as some terms need not be entered in the search query. Rather, the filters act as a substitute for certain terms. For example, instead of adding the term 'clinical trial' to a search query, a user can simply select the methods filters, which would limit MEDLINE to those studies using best methods for questions of therapy (*i.e*., randomized clinical trials). Thus, when we add the methods and/or renal content filters to physician searches, we will need to remove any methods and/or renal content terms in the physician's search query. To do so, each search query will be reviewed independently and in duplicate by two assessors trained in epidemiology and by two assessors trained in medicine. Discrepancies in decisions to remove terms by the assessors will be resolved by consensus.

### Example

Clinical Question: What are the benefits of intradermal compared to intramuscular hepatitis B vaccination in chronic kidney disease?

Search query provided by a physician: hapititis b vaccination dialysis randomized trial

Modified search query as per listed rules: hepatitis b vaccination dialysis randomized trial

Query aided by methods filter: hepatitis b vaccination dialysis AND <methods filter>

Query aided by content filter: hepatitis b vaccination randomized trial AND <content filter>

Query aided by methods and content filter: hepatitis b vaccination AND <methods filter> AND <content filter>

Due to the large number of PubMed searches required (9 searches × 100 clinical questions = 900 searches), the searching process will be automated through the use of the E-utilities resource available from PubMed[53]. We have tested this process and confirmed that the results retrieved through E-utilities match those retrieved using the PubMed interface. For each search, we will collect the total number of articles retrieved and the number of relevant articles retrieved. To determine the latter, we will compare the PubMed unique identifiers of the retrieved articles to the PubMed identifiers of the relevant articles identified from the systematic review for the specified clinical question. We will restrict each search to the search dates provided in the methods section of each systematic review; date restriction will be used to exclude articles, both relevant and non-relevant, that could not have been included in the systematic review process.

### General statistical analytic strategy, sample size, and sensitivity analyses

#### Primary analysis

We will calculate differences in recall between every physician's unaided search, and the physician's searches when each of eight filter combinations is applied. We will use a two-sided one-sample (paired) t-test for each filter combination to determine if a difference exists (Null Hypothesis, H_0_: mean difference in recall between unaided search and search with filter = 0, Alternate Hypothesis, H_1_: mean difference in recall not = 0). We will then rank the performance of each filter combination that enhanced the unaided search, and examine this list descriptively. We may perform additional post-hoc t-tests amongst top performing filter combinations to determine which combination was the best. We will then repeat this entire statistical process for the outcome precision. Filter combinations that improve both recall and precision (best-performing filter combinations) will be examined descriptively. A large number of significance tests will be conducted in this study (eight tests for recall, eight tests for precision, total 16 tests). To reduce the risk of type I error, we will apply the conservative method of Bonferroni so that tests with a p < 0.003 will be interpreted as statistically significant[54].

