#### Sample size

We expect to identify 100 systematic reviews that meet our criteria. Using our pilot data, we estimate a standard deviation of 0.23 for the difference in recall, and a standard deviation of 0.34 for the difference in the precision. Given a sample of 100 clinical question responses (with each nephrologist receiving a single unique question) power of 80% and a significance p-value of 0.003, using a two-sided one-sample t-test, we will have the ability to detect a minimum of 9.0% mean difference in recall and a 13.2% mean difference in precision between a filtered search and an unaided search. These values represent a reasonable benefit to warrant the ongoing effort to incorporate the filters into use. Sample size calculations were performed using SAS Statistical Package version 9.1 (SAS Institute Inc., Cary, NC, and U.S.A.).

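### Holm's step-down procedure would give the 16 primary tests the same familywise error guarantee as the fixed p < 0.003 cut-off, with equal or higher power

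*Protocol article*

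**What the plan says.** The Primary analysis section of the protocol article compares each of eight filtered searches with the physician's unaided search: "We will use a two-sided one-sample (paired) t-test for each filter combination to determine if a difference exists". This is done for recall and then repeated for precision, and the section counts the family itself: "eight tests for recall, eight tests for precision, total 16 tests". For multiplicity it states: "we will apply the conservative method of Bonferroni so that tests with a p < 0.003 will be interpreted as statistically significant". The aim given there is to reduce the risk of type I error. No overall level is stated and no reason is given for a single-step rule.

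The Sample size section works at the same cut-off. Its inputs are "Given a sample of 100 clinical question responses", "we estimate a standard deviation of 0.23 for the difference in recall", "a standard deviation of 0.34 for the difference in the precision" and "power of 80% and a significance p-value of 0.003, using a two-sided one-sample t-test". It concludes "we will have the ability to detect a minimum of 9.0% mean difference in recall", with 13.2% as the corresponding figure for precision.

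The Hypotheses section expects filters to improve searches in general, with the largest improvement from combining the two filter types.

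**The concern.** A single-step rule holds every test to 0.003, however many of the others have already been rejected. A step-down rule relaxes the threshold as rejections accumulate and gives the same familywise guarantee with no added assumption. The difference is small when few effects are real and grows as more become real. The plan's own hypothesis is that filters help generally, so it may be operating where the fixed cut-off costs most. The tests are two-sided, so a filter that lowers recall also counts as a rejection and would relax the later thresholds.

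At stake is power for the statements of statistical significance. A combination whose true effect equals the difference that the plan set out to detect could fall short of 0.003 when an equally protective rule would have declared it.

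**Working it through.** **Inputs.** From the Primary analysis section: 16 tests, two-sided paired t-test, cut-off 0.003. From the Sample size section: n = 100, SD 0.23 (recall) and 0.34 (precision), 80% power. Assumed: an overall level of 0.05, because 0.05/16 = 0.003125, which rounds to 0.003, and 16 × 0.003 = 0.048.

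**1. The plan's own figures.** Power is that of a two-sided one-sample t-test with 99 degrees of freedom and noncentrality δ√n/SD. At the stated differences the noncentrality is 0.090 × 10/0.23 = 3.91 for recall and 0.132 × 10/0.34 = 3.88 for precision. At alpha 0.003 this gives power of 80.5% and 79.6%. Solving for exactly 80% gives detectable differences of 0.0896 and 0.1325. The stated 9.0% and 13.2% reproduce.

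**2. Holm's rule.** Order the 16 p-values. Compare the k-th smallest with 0.05/(16 − k + 1) and stop at the first failure.

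- *Never fewer rejections.* Every threshold is at least 0.05/16 = 0.003125, which exceeds 0.003. Any test with p < 0.003, and every test with a smaller p, therefore passes.
- *Same error control.* Suppose m₀ nulls are true. When the first true null is rejected, at least m₀ hypotheses are still in play, so its threshold is at most 0.05/m₀. The chance that any of the m₀ true nulls has a p-value that small is at most m₀ × 0.05/m₀ = 0.05, whatever the correlation.

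**3. Power at selected Holm steps, at the plan's stated differences**

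| Step | Threshold | Power, recall | Power, precision | Detectable at 80% (recall / precision) |
|---|---|---|---|---|
| 1 | 0.003125 | 80.8% | 80.0% | 0.0893 / 0.1320 |
| 9 | 0.00625 | 86.5% | 85.9% | 0.0838 / 0.1239 |
| 16 | 0.05 | 97.2% | 97.0% | 0.0651 / 0.0962 |

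A later step is reached only if all the earlier ones reject, so the procedure as a whole needs simulation.

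**4. Simulation of the whole procedure.** There were 6,000 trials per scenario, with n = 100 and 16 paired t-tests. Each true effect was set at the plan's detectable difference. The within-outcome correlation was 0 or 0.5 (assumed), with recall and precision independent (assumed). Each cell shows correlation 0 / 0.5.

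| True effects (recall + precision) | Power at p < 0.003 | Power with Holm | Familywise error with Holm |
|---|---|---|---|
| 0 | – | – | 5.3% / 3.9% |
| 1 (1 + 0) | 81.3% / 80.2% | 81.7% / 80.8% | 5.0% / 3.7% |
| 4 (2 + 2) | 79.7% / 79.6% | 81.7% / 81.3% | 4.5% / 4.1% |
| 8 (4 + 4) | 80.2% / 79.9% | 84.6% / 84.0% | 4.3% / 3.0% |
| 12 (6 + 6) | 80.0% / 80.2% | 88.0% / 87.3% | 3.9% / 3.3% |
| 16 (8 + 8) | 80.2% / 80.3% | 94.8% / 92.9% | no true nulls |

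The 5.3% (0.0525) in the all-null, uncorrelated case has a simulation standard error of about 0.003. It is identical to single-step Bonferroni at 0.05/16 in the same runs, so it is simulation noise. In every simulated trial Holm rejected all that Bonferroni at 0.05/16 rejected. Roughly 0.3 to 0.5 points of each gain comes only from rounding 0.003125 down to 0.003.

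**5. A mixed scenario.** Twelve of the 16 effects are real. Eight sit at the detectable differences and four are larger (0.15 and 0.12 for recall, 0.25 and 0.20 for precision). With correlation 0.5, power for the eight rises from about 80% to about 88%. Familywise error is about 1.2% under Bonferroni and 3.8% under Holm.

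**The case against.** The strongest reply is that nothing here is wrong. Bonferroni is valid, its conservatism is declared, the family is counted correctly, and the study is sized at the cut-off that it uses. All of that stands. A reader might infer that the sample size statement is faulty or that the tests are invalid, and the documents support neither reading.

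Second, the gain depends on how many effects are real. The article gives no pilot mean effects, and a hypothesis that filters help is not an estimate that most of the 16 nulls are false. This also stands, so the gain has to be given as a range and not by one favourable scenario.

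Third, a reader might infer that the cut-off decides which filters appear on the ranked list. The Primary analysis section does not say so. It ranks the combinations that enhanced the unaided search and examines the list descriptively, and it treats those that improve both outcomes in the same way. Entry is not tied to p < 0.003. What the cut-off decides is the label of statistical significance.

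Fourth, Holm has costs. The realised familywise error moves closer to 5%, and a recall verdict can depend on precision p-values. Holm also has no equally simple matching simultaneous intervals, so a Holm-significant result could carry a Bonferroni-level interval that includes zero. These are real but small. The error stays within the intended 5%, the article itself treats the 16 tests as one family, and it describes no simultaneous intervals.

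**Conclusion.** The point holds as an efficiency improvement that is nearly free, not as an error. On the same 16 tests Holm gives the same guarantee at 0.05 under any dependence and cannot lose a rejection. At the plan's own SDs and detectable differences, the gain in power per true effect is under 1 point with one true effect, about 2 with four, about 4 with eight, 7 to 8 with twelve and about 13 to 15 with all sixteen.

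These sizes rest on the assumed overall 0.05, on true effects set exactly at the stated detectable differences, on the two correlation values, and on an unknown number of true effects. The fact that Holm never rejects less rests on none of the last three. The consequence is limited to which combinations are declared statistically significant.

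**What to change.** In the Primary analysis section, replace the Bonferroni sentence with: *The 16 primary tests will be judged by the Holm step-down procedure at an overall two-sided 0.05 (smallest p-value against 0.05/16, the next against 0.05/15, and so on, stopping at the first failure).* This also states the overall level, which at present has to be inferred.

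In the Sample size section, keep 9.0% and 13.2% and describe them as the worst case, since the first Holm step is in effect the present cut-off. The Secondary analysis is defined as identical to the primary one apart from the cut-point, so it would inherit the rule.

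The cost is one sentence, settled before the results are seen, with no change to sample or data. If Bonferroni-level intervals are reported, add that significance is decided by the Holm-adjusted p-values, so that an interval including zero beside a significant result is not read as a contradiction.

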#### Secondary analysis

We will use the responses provided by nephrologists to determine the number of results that three-quarters of the respondents do not scan beyond. This number will be rounded to the closest multiple of 20. A value of 20 is used because it reflects one page of search results in PubMed on the default setting. For example, if 75% of the respondents indicate they do not look beyond 52 results, we would use 60 as a cut-point to signify three search pages in PubMed. This secondary analysis will be identical to the primary analysis except that we will calculate the values of recall and precision limited to citations within the defined cut-point. For example, for a cut-point of 60 results, the measures would be calculated for articles retrieved in the first 60 results (or three default pages of results).

#### Other analysis

We will analyze the baseline characteristics of non-responding physicians, compared to physicians who do respond, to elucidate systemic non-response and aid with conclusions of generalizability.

#### Sample size

We expect to identify 100 systematic reviews that meet our criteria. Using our pilot data, we estimate a standard deviation of 0.23 for the difference in recall, and a standard deviation of 0.34 for the difference in the precision. Given a sample of 100 clinical question responses (with each nephrologist receiving a single unique question) power of 80% and a significance p-value of 0.003, using a two-sided one-sample t-test, we will have the ability to detect a minimum of 9.0% mean difference in recall and a 13.2% mean difference in precision between a filtered search and an unaided search. These values represent a reasonable benefit to warrant the ongoing effort to incorporate the filters into use. Sample size calculations were performed using SAS Statistical Package version 9.1 (SAS Institute Inc., Cary, NC, and U.S.A.).

#### Sensitivity analyses

In the primary analysis of this study, we will consider each article listed in a systematic review as equally important. However we recognize that some articles may be considered more important and influential than others, and a searcher may be most interested in identifying these seminal articles. To address this point, we will perform sensitivity analyses to test whether filters help identify the most important articles, as defined by two different criteria as outlined below.

##### Criterion one: Articles referenced in UpToDate

This analysis will focus on the articles listed in the systematic reviews that are referenced in UpToDate. For each review, two assessors will independently conduct a search in UpToDate using the objective statement of the review as a guide. The assessors will document the entries that cover the review topic; each search may recover several UpToDate entries. All entries will be compiled and an assessor will evaluate each entry to determine whether included studies from the review were referenced; each referenced article will be tagged as an important article for the current analysis. Finally, systematic review topics not covered in UpToDate will be excluded from analysis.

##### Criterion two: Highly cited articles

This analysis will focus on the top cited articles from each systematic review. For each article, we will search Web of Science to identify the number of times the article was cited by other publications. If Web of Science does not provide a citation count, we will then search Scopus. If Scopus fails to provide a citation count, we will search Google Scholar. If none of the sources provide a citation count, the article will be assigned a citation count of one because we are certain that the study was cited by at least one systematic review. After retrieving all citation counts, we will tabulate the median citation count for all articles included in each systematic review. Articles with citation counts greater than or equal the median value will be tagged as important articles in each systematic review for the current analysis.

### Other considerations

#### Minimizing threats to validity

Our protocol has adapted methodology originating from the field of information retrieval. We have attempted to control for the following biases identified in previous studies on search engine evaluation[55,56]:

Suggestion: To ensure internal validity, a sufficiently large number of search topics must be used to produce meaningful evaluations of search engine effectiveness.

Solution: We will use 100 recently published systematic reviews in nephrology to assemble a variety of clinical questions and identify corresponding sets of relevant articles.

Suggestion: To ensure external validity, search topics should be motivated by the genuine information needs of the target users.

Solution: We will identify renal systematic reviews. Systematic reviews target questions for which uncertainty exists and are of interest to nephrologists.

Suggestion: To ensure external validity, search queries used to evaluate the retrieval quality should be derived by individuals in the target population.

Solution: Through the use of a survey, we will obtain search queries from practicing nephrologists.

Suggestion: To ensure overall validity, relevance judgments must be made in relation to the target population.

Solution: We will use the primary articles included in high quality systematic reviews to identify relevant literature. Through this procedure, we are engaging widely accepted principles of evidence-based medicine to identify the most important primary literature to retrieve in a search. We will select those systematic reviews that detail reliable and comprehensive methods of assembling relevant articles for a focused therapy question; this will help ensure all sound evidence is accounted for, minimizing subjectivity in the selection of relevant studies.

Furthermore, several other methods to avoid bias and maximize generalizations will be used:

1. To avoid misclassification of the outcome, we will record the date for which information was compiled in each review and subsequently limit all searches to the appropriate start and end dates. Date restriction will be used to preclude articles, both relevant and non-relevant, not considered in the systematic review process. In addition, we will only include primary studies that are indexed in PubMed.

2. By ensuring that each included systematic review targets only one objective, the study will further minimize misclassification by ensuring that all included articles in the review are truly relevant for the corresponding treatment question.

3. We will minimize selection bias by random, rather than convenience sampling, to select Canadian nephrologists for survey participation. This will ensure that a large variety of nephrologists with varied search abilities participate in the study. Clinical questions will be randomly assigned to each nephrologist ensuring that, on average, physicians have equal familiarity with the topic. We will also evaluate the characteristics of non-responding physicians to physicians for whom responses are received to identify potential systemic non-response that may impair the random nature of the responses.

4. For the survey, we will employ the tailored design method to maximize response[46].

5. When testing the impact of filter usage, we will adjust the alpha level of significance to avoid detecting spurious associations (type I errors) through multiple statistical comparisons.

6. We will employ a paired design to ensure equivalence in potential biases between the unaided and filter-aided searches.

### Additional considerations

#### Determining article relevancy

There is no perfect, easily applied measure to determine whether an article is relevant to a focused clinical question. We propose to use primary articles identified in systematic reviews, as an external measure of relevance in this study. All other articles will be viewed as non-relevant. We recognize there are additional articles, such as commentaries, narrative reviews, case reports, and animal studies which some may consider relevant. However, by using systematic reviews to define relevance, we are engaging widely accepted principles of the hierarchy of evidence to identify the most important articles to retrieve in a search. Also, our primary analytic method is a 'paired design' where we compare physician search performance with and without the use of filters. Any misclassification of article relevance is expected to impact all the queries in a similar manner, with no major effect on differences observed between search strategies.

#### Performance metrics

In this study, we will use recall and precision as metrics to determine how well a reference set of relevant articles are retrieved. Some may say this is a misleading surrogate outcome. We agree that other more relevant outcomes would be desired. For example, it would be useful to know whether the use of filters improves a physician's ability to come up with the correct answer (better knowledge), whether this changes medical decisions or processes of care, and whether this improves patient outcomes. The current study represents a key milestone in a staged program of research, to guide the development and execution of future studies (Table 4).

#### Systematic reviews focus on questions of therapy

Currently, most systematic reviews pertain to prevention and treatment. For reasons of feasibility, we are only testing methods filters related to therapy in this project. However, more systematic reviews for diagnosis, prognosis, and etiology are being published every day. This will allow us to reliably assess other methods filters in the future.

#### Searching is a dynamic process

The initial search queries we receive from physicians will be entered online, or received by mail. In truth, searching is a dynamic process -- an unsuccessful search is tried again using different terms. Also, what physicians report in a survey may differ from what they do in front of their own computers. We did consider a different research framework, such as video surveillance of local nephrologists using MEDLINE filters. However, for reasons of feasibility and generalizability, we propose to obtain the initial search queries from a random sample of nephrologists practicing in academic and non-academic settings across Canada. We are testing their first search. If filters substantially improve search performance we may obviate the need for additional searches, saving time and reducing frustration.

